## Abstract

Coronary artery disease (CAD) is a major contributor to morbidity and mortality worldwide. Myocardial ischemia may occur in patients with normal or non-obstructive CAD on invasive coronary angiography (ICA). The comprehensive evaluation of coronary CT angiography (CCTA) integrated with fractional flow reserve derived from CCTA (CT-FFR) to CAD may be essential to improve the outcomes of patients with non-obstructive CAD. China CT-FFR Study-2 (ChiCTR2000031410) is a large-scale prospective, observational study in 29 medical centers in China. The primary purpose is to uncover the relationship between the CCTA findings (including CT-FFR) and the outcome of patients with non-obstructive CAD. At least 10,000 patients with non-obstructive CAD but without previous revascularization will be enrolled. A 5-year follow-up will be performed. The primary endpoint is the occurrence of major adverse cardiovascular events (MACE), including all-cause mortality, non-fatal myocardial infarct, unplanned revascularization, and hospitalization for unstable angina. Clinical characteristics, laboratory and imaging examination results will be collected to analyze their prognostic value.

## Introduction

Cardiovascular disease is a worldwide disease, but China is one of the countries with the heaviest disease burden (1). Since the 1980s, the burden of ischemic heart disease (IHD) in China has been increasing and has become more marked in the past 20 years (2). In 2013, IHD was reported to be the leading cause of death in six provinces, accounting for ~78% of the Chinese population (3). Moreover, IHD was ranked as the second leading cause of premature death in 2010 (2). The assessment and management of patients with coronary artery disease (CAD) have always focused on detecting and treating obstructive coronary artery stenosis (i.e., lumen obstruction of >50% [or >70%] by visual assessment) (4). However, the patients with CAD often are asymptomatic prior to myocardial infarction (MI), and coronary death with culprit lesions that are often non-obstructive before the events (5–7). The risk of cardiovascular events in patients with non-obstructive CAD is significantly higher than in patients without CAD (8, 9). Recently, the value of non-obstructive CAD and high-risk plaque (HRP) has been established (10).

Coronary CT angiography (CCTA) is a widely used non-invasive imaging modality to evaluate CAD and has demonstrated a high diagnostic performance in detecting obstructive and non-obstructive CAD on invasive coronary angiography (ICA) (11). Likewise, CCTA can also identify HRP seen on intravascular ultrasound or optical computed tomography (12). Coronary artery data and reporting system (CAD-RADS) has been reported to provide additional prognostic value beyond a coronary artery calcium score (CACS) and atherosclerotic cardiovascular disease (ASCVD) risk score (13). However, this reporting system does not consider the functional information of CAD, which is more important to determine the physiological nature of coronary stenoses than the anatomy (14). A previous study showed that 35% of non-obstructive CAD (diameter stenosis < 50%) was associated with ischemia (fractional flow reserve [FFR] ≤ 0.80), while 20% of lesions with >50% stenosis had no ischemia (15).

Coronary CT angiography-derived FFR (CT-FFR) has been reported to be a potential alternative to provide a physiological evaluation of the entire coronary artery tree, with high diagnostic accuracy in stable CAD patients compared with invasive FFR, the gold standard (16). Moreover, CCTA combined with selective CT-FFR is shown to be associated with a safety reduction of unnecessary ICA and relevant costs when compared with standard clinical practice (17). According to the ADVANCE (18) trial, patients with a negative CT-FFR have less revascularization and a trend toward lower major adverse cardiovascular events (MACE) and significantly lower MI or cardiovascular death. We hypothesize that integrating CCTA with CT-FFR will improve the recognition of subclinical plaques, optimize the risk stratification, and improve the prognosis of patients with non-obstructive CAD. Therefore, a large prospective study cohort from 29 medical centers in China (China CT-FFR Study-2) is designed to verify this hypothesis through a 5-year long-term follow-up.

The aims of this study are to (1) establish a large cohort of patients with non-obstructive CAD based on the Chinese population and conduct a long-term follow-up observation and (2) explore the predictive value of CT-FFR for MACE in patients with non-obstructive CAD beyond the clinical and anatomical factors.

## Methods and Analysis

### Study Design

This is a prospective, observational, multicenter registry study. The trial protocol and written informed consent forms have been reviewed and approved by the clinical trial ethics committee at Jinling Hospital, Medical School of Nanjing University (General Hospital of Eastern Theater Command), and by each center before the initiation of the investigation. All enrolled patients will provide written informed consent at admission for their data collection and utilization for future anonymous studies. The study has been registered on http://www.chictr.org.cn (ChiCTR2000031410). This study is partially supported by the National Key Research and Development Program of China (no. 2017YFC0113400), Jiangsu Provincial Key Research and Development Program (no. BE2020699), and Key Program of the National Natural Science Foundation of China (no. 81830057) for [name].

### Selection of Subjects

We aim to include ten thousand patients referred for CCTA examination by physicians for the evaluation of suspected or known CAD and subsequently diagnosed as non-obstructive CAD by CCTA (defined as a coronary artery stenosis [maximal stenosis] greater than or equal to 20% but <50% [for left main coronary artery] or greater than or equal to 20% but <70% [for any other epicardial coronary artery] in vessel segments ≥1.5 mm diameter) (19) but without previous revascularization (percutaneous coronary intervention [PCI] or coronary artery bypass grafting [CABG]). The enrollment process is shown in Figure 1.

**Figure 1 F1:**
[figure not shown]
Patient enrollment flow chart. CCTA, coronary computed tomography angiography; PCI, percutaneous coronary intervention; CABG, coronary artery bypass grafting.

### Inclusion Criteria

1) The patient must sign a written informed consent before any study procedures.2) Non-obstructive coronary CAD by CCTA (a coronary artery stenosis [maximal stenosis] ≥20% but <50% [for left main coronary artery] or ≥20% but <70% [for any other epicardial coronary artery] in vessel segments ≥1.5 mm diameter).

### Exclusion Criteria

1) Refusal to participate.2) <18 years or >80 years.3) Pregnancy or lactation.4) Allergy to iodinated contrast agents.5) Previous revascularization (PCI or CABG).6) Previous cardiac transplantation or valvular surgery.7) Any life-threatening condition or severe co-morbidity.8) Patients with poor image quality studies, unsuitable for further analysis.9) Coronary artery fistula and anomalous origin.10) Complex congenital heart disease.11) Missing data.

During the initial screening stage (conducted by each center), any patients who meet any one of the above 1-7 exclusion criteria will be excluded. The final enrollment will be determined by the core laboratory (Jinling Hospital, Medical School of Nanjing University) after double-checking the data, re-evaluating coronary artery stenosis and image quality.

## Study Procedures

### Clinical Variables

Baseline clinical characteristics will be obtained through an electronic questionnaire for each participating patient at enrollment, including age, sex, height, weight, diabetes mellitus, hypertension, hyperlipidemia, smoking, drinking, positive CAD family history, clinical symptoms, all patient-reported examinations, medications, and surgeries associated with the cardiovascular disease within 6 months (Tables 1–5). Diabetes mellitus is defined as a history of diabetes mellitus diagnosed or treated by a physician, treated with oral antidiabetic therapy, or an admission fasting blood glucose level ≥126 mg/dl. Hypertension is defined as a history of high blood pressure diagnosed or treated by a physician, treated with antihypertensive therapy, or an admission blood pressure ≥140/90 mmHg. Dyslipidemia is defined as a history of hyperlipidemia diagnosed or treated by a physician, being in treatment with antihyperlipidemic drugs, or admission total cholesterol (TC) ≥200 mg/dl. Smoking/drinking is defined as current smoker/drinker or prior smoker/drinker within the last year. Positive CAD family history is defined as cardiac death or MI in first-degree relatives (<55 years in men or <65 years in women). Chest pain will be recorded and classified as typical angina, atypical angina and non-anginal chest pain according to the site, characteristics and duration of the chest discomfort and its relationship with exercise, and the inducing and relieving factors (20). Typical angina is considered to meet the following three characteristics: (a) constricting discomfort in the front of the chest or in the neck, jaw, shoulder, or arm; (b) induced by excessive physical activity; and (c) relieved by rest or nitrates within 5 min. Patients presenting with two of the aforementioned typical angina features are considered to have atypical angina. Patients presenting with only one or none of the typical angina characteristics are supposed to have non-anginal chest pain. Relevant medications will be recorded as statin, antiplatelet, beta-blockers, angiotensin-converting enzyme inhibitors (ACEI), angiotensin-receptor blockers (ARB), oral hypoglycemic agent, insulin, oral anticoagulation, calcium channel blocker (CCB), and diuretic. In addition, laboratory test results for C-reactive protein, triglycerides, TC, low-density lipoprotein cholesterol (LDL-C), high-density lipoprotein cholesterol (HDL-C), and cardiac enzyme level will be collected, if possible. The Framingham risk score (FRS) will be calculated for subjects with the complete information of age, sex, TC, HDL-C, systolic blood pressure, diabetes mellitus, antihypertensive medication, and smoking status (21). Meanwhile, the Multi-Ethnic Study of Atherosclerosis (MESA) score will also be calculated using age, gender, race/ethnicity, diabetes mellitus, smoking status, TC, HDL-C, antihyperlipidemic drugs, and MI family history (22).

**Table 1 T1:** Baseline demographic information.

Name: _________________ ID number:______________
Birthday:_________________ Sex: □Male □Female
Height: cm Weight: kg
Telephone number (participant):_________________
Telephone number (first relatives):_________________
Relationship between relatives and participant:_______________

*ID, Identity document; cm, centimeter; kg, kilogram*.

**Table 2 T2:** Baseline clinical information.

1. Hypertension: □Yes □No (meet one of the following three factors)
□systolic blood pressure ≥140 mmHg
□diastolic blood pressure ≥90 mmHg
□being treated with antihypertensive therapy
2. Diabetes mellitus: □Yes □No (meet one of the following two factors)
□fasting blood glucose level ≥126mg/dl
□being treated with oral antidiabetic therapy
3. Dyslipidemia: □Yes □No (meet one of the following two factors)
□total cholesterol ≥200mg/dl
□being treated with antihyperlipidemic drugs
4. Smoking: □Yes □No (meet one of the following two factors)
□current smoker
□previous smoker within the last year
5. Drinking: □Yes □No (meet one of the following two factors)
□current drinker
□previous drinker within the last year
6. Positive family history: □Yes □No (meet one of the following two factors)
□cardiac death or MI in first-degree relatives younger than 55 years in men
□cardiac death or MI in first-degree relatives younger than 65 years in women
7. Clinical symptoms:
□chest pain: □in the front of the chest or in the neck, jaw, shoulder, or arm
□precipitated by physical exertion
□relieved by rest or nitrates within 5 min
□palpitation □dyspnea □syncope □other

*MI, myocardial infarction*.

**Table 3 T3:** Baseline medications information.

Whether there is a history of cardiovascular disease-related drug use within 6 months before the examination: □Yes □No (If yes, continue to fill in the content below)
□statin: dose:________ duration: from_____to
□antiplatelet: dose:________duration: from_____to
□beta-blocker: dose:________ duration: from_____to
□ACEI: dose:________duration: from_____to
□ARB: dose:________ duration: from_____to
□CCB: dose:________duration: from_____to
□diuretic: dose:________ duration: from_____to
□oral hypoglycemic agents: dose:________ duration: from_____to
□insulin: dose:________ duration: from_____to
□oral anticoagulation: dose:________duration: from_____to
□other: dose:________ duration: from_____to

*ACEI, angiotensin converting enzyme inhibitor; ARB, angiotensin-receptor blocker; CCB, calcium channel blocker*.

**Table 4 T4:** Baseline surgical information.

Whether there is a history of cardiovascular disease-related surgeries within 6 months before the examination: □Yes □No (If yes, continue to fill in the content below)
1. Surgical method:
Surgical date:
Postoperative diagnosis:
2. Surgical method:
Surgical time:
Postoperative diagnosis:
3. Surgical method:
Surgical time:
Postoperative diagnosis:
4. Surgical method:
Surgical time:
Postoperative diagnosis:
……

**Table 5 T5:** Baseline imaging tests information.

Whether there is a history of cardiovascular disease-related imaging examinations before the examination: □Yes □No (If yes, continue to fill in the content below)
1. Examination method: □CT □MRI □OCT □PET □SPECT □other
time:__________ region:
diagnosis:
2. Examination method: □CT □MRI □OCT □PET □SPECT □other
time:__________ region:
diagnosis:
3. Examination method: □CT □MRI □OCT □PET □SPECT □other
time:__________ region:
diagnosis:
4. Examination method: □CT □MRI □OCT □PET □SPECT □other
time:__________ region:
diagnosis:
5. Examination method: □CT □MRI □OCT □PET □SPECT □other
time:__________ region:
diagnosis:
……

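### As printed, the baseline data items do not match the inputs of the Framingham and MESA scores that the protocol says will be calculated

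*Protocol article*

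**What the plan says.** The Clinical Variables section sets out how baseline data are captured: "Baseline clinical characteristics will be obtained through an electronic questionnaire for each participating patient at enrollment", with Tables 1–5 cited as the content. The same section then commits to two clinical risk scores.

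- **Framingham.** Calculated for subjects with "complete information of age, sex, TC, HDL-C, systolic blood pressure, diabetes mellitus, antihypertensive medication, and smoking status".
- **MESA.** Calculated from "age, gender, race/ethnicity, diabetes mellitus, smoking status, TC, HDL-C, antihyperlipidemic drugs, and MI family history".

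On blood pressure, the text gives only a threshold within the definition of hypertension, "an admission blood pressure ≥140/90 mmHg". Table 2 has a matching box, "systolic blood pressure ≥140 mmHg", a second box for diastolic pressure at 90 mmHg, and a third for treatment. None has room for a value.

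On family history, the text reads "Positive CAD family history is defined as cardiac death or MI in first-degree relatives (<55 years in men or <65 years in women". Table 2 follows it with two boxes, of which the first is "cardiac death or MI in first-degree relatives younger than 55 years in men" and the second is the same item for women with a limit of 65.

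**The concern.** A score defined only for people with complete inputs needs every input to be collected. Here the article prints both the list of score inputs and the baseline fields, and the two do not line up. If sites collect only what is printed, no systolic value in mmHg reaches the database, and the Framingham score lacks a required input. The MESA input named as family history of MI would have to be taken from an item that mixes two kinds of event and applies age limits.

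The scores have a plausible use. The second aim, in the Introduction, is the predictive value of CT-FFR beyond clinical and anatomical factors, and these are the only two clinical risk scores named for calculation in Clinical Variables. A baseline reading that was never written down cannot be taken again later. It can only be retrieved from records.

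**Working it through.** The protocol states no figure on this point, so the check sets each named score input against the fields in Clinical Variables and Tables 1–5.

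| Input | Framingham | MESA | Where it is listed | Usable as listed? |
|---|---|---|---|---|
| Age | yes | yes | Table 1, from birthday | yes |
| Sex | yes | yes | Table 1 | yes |
| Total cholesterol | yes | yes | Tick box in Table 2, and laboratory result in the text, if possible | yes, through the laboratory result |
| HDL cholesterol | yes | yes | Laboratory result in the text, if possible | yes |
| Diabetes | yes | yes | Table 2 | yes |
| Smoking | yes | yes | Table 2, current and within the last year ticked separately | yes |
| Antihypertensive treatment | yes | – | Tables 2 and 3 | yes |
| Lipid-lowering treatment | – | yes | Table 2; statin in Table 3 | yes |
| Systolic pressure | yes | – | Tick box at 140 mmHg in Table 2; threshold in the text | no value listed |
| Family history of MI | – | yes | Pooled with cardiac death, limits 55 and 65 | proxy only |
| Race/ethnicity | – | yes | Nowhere in Tables 1–5 or the collection text | not listed |

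**Counts.** Framingham: 8 inputs, 7 usable, so 8 − 7 = 1 gap (systolic pressure). MESA: 9 inputs, 7 usable, so 9 − 7 = 2 gaps (family history of MI, race/ethnicity).

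**Cholesterol as the contrast.** Table 2 also reduces total cholesterol to a tick box, at 200 mg/dl, but the text separately lists it as a laboratory result to be collected. Systolic pressure has no such second route. Tables 1 and 3 show that the form does give open fields where a value is wanted: height, weight, drug dose and dates.

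**What the family-history item does.** The boxes separate relatives by sex and age limit, not by event. A father's MI at 60 is entered as negative, because 60 is above 55. A brother's cardiac death at 50 without MI is entered as positive. Neither entry can be undone afterwards, because neither the event type nor the age at event is recorded.

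**The case against.** The strongest reply is that the printed tables are not the whole data set. HDL cholesterol, LDL cholesterol, triglycerides and C-reactive protein are in none of Tables 1–5, yet the text says they will be collected. Data Collection and Management describes a web-based case report form with broad scope whose item list is not shown, and a journal article commonly leaves field-level detail to it. The hypertension definition presupposes a measured admission pressure, and the Framingham sentence itself allows for incomplete subjects. This stands to the extent that silence does not prove that the value goes unrecorded. It does not remove the mismatch, because the other laboratory inputs are named in the collection text and systolic pressure is not.

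On MESA, the phrase about family history may be shorthand for the study's own item, and the score's definition is not in the protocol. That also stands: whether the pooled item departs from what the score requires cannot be settled here. The missing race/ethnicity field may matter little in a cohort described in the Introduction as based on the Chinese population, but the protocol does not say that one category will be assumed.

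A reader might go further and infer that a weakened clinical comparator would make CT-FFR look better than it is. The protocol does not support this. Data Analysis mentions neither score, makes neither the base model, and speaks only of Cox models of variables and AUCs for each model. Individual clinical factors can enter those models without either score. Nor does the protocol propose using the tick box in place of the systolic value.

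**Conclusion.** The point holds in a conditional form. As printed, the baseline items fall short of the named inputs by 1 of 8 for Framingham and 2 of 9 for MESA. Unless the full case report form already holds the missing items, the Framingham score cannot be calculated from the listed fields, and MESA would use a proxy for family history and an unstated race/ethnicity category.

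The conclusion rests on one assumption, that sites collect what the article lists. A reader might infer that the Framingham score is certainly unavailable for every patient. That does not follow, because the full form is not shown and the reading has to be taken to complete the tick box.

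The consequence is limited to two scores that the protocol commits to calculating. The primary endpoint and the sample size are not affected. The point is worth acting on because the correction is specific and cheap.

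**What to change.** 1. Add numeric systolic and diastolic pressure in mmHg, taken from the admission reading already needed for the tick boxes. For patients already enrolled, retrieve the reading from admission records.
2. Record family MI and family cardiac death as separate items, each with the relative's sex and age at event. Both the study's own definition and a family history of MI can then be derived. For patients already enrolled, the annual telephone call is a natural occasion to ask.
3. Add race/ethnicity, or state that one category is assumed for all subjects when MESA is calculated.
4. If the case report form already collects any of these, correct the printed form and the text of Clinical Variables so that they agree with the score inputs.

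The cost is a few extra fields and some site time for retrospective completion. Some older readings may prove irretrievable. The existing restriction of the Framingham score to subjects with complete information already covers those patients.

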### Secondary Endpoints

Secondary endpoints include cardiovascular death, atrial fibrillation, non-fatal MI, non-fatal stroke, unplanned revascularization, hospitalization for unstable angina, medication adjustment, invasive or non-invasive cardiovascular tests, cumulative radiation exposure from all cardiovascular tests, and total cardiac costs. Medication adjustment includes the increase or decrease of the drug dose and the new addition or discontinuation of medications. For the secondary endpoints, the time of the occurrence for any one of the above events should be recorded.

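### The Table 2 baseline form drops the physician-history route that the Methods allow for diabetes, hypertension and dyslipidaemia, so some patients are Yes by the Methods and No on the form

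*Protocol article*

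**What the plan says.** The protocol article, under Clinical Variables, defines the three risk factors in prose. For diabetes: "Diabetes mellitus is defined as a history of diabetes mellitus diagnosed or treated by a physician, treated with oral antidiabetic therapy", with a raised admission fasting glucose as a further alternative. For hypertension: "Hypertension is defined as a history of high blood pressure diagnosed or treated by a physician", with antihypertensive treatment or a raised admission pressure as alternatives. Dyslipidaemia has the same structure: a diagnosed or treated history, lipid-lowering drugs, or total cholesterol of at least 200 mg/dl. The section says that baseline characteristics come from an electronic questionnaire and points to Tables 1–5.

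Table 2 prints the corresponding items. The diabetes item is "Diabetes mellitus: □Yes □No (meet one of the following two factors". Its two factors are fasting glucose of at least 126 mg/dl and "being treated with oral antidiabetic therapy". The hypertension item offers systolic pressure of at least 140 mmHg, diastolic pressure of at least 90 mmHg, or current drug treatment. The dyslipidaemia item offers total cholesterol of at least 200 mg/dl or current drug treatment. None of the three has a box for a physician's diagnosis. Insulin appears only in Table 3, among drugs used in the six months before the examination: "insulin: dose:________ duration: from_____to". The article does not say that this entry feeds the diabetes item.

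**The concern.** Two stated rules for the same variable disagree, and the narrower one is printed on the form that centres fill in. If staff follow the form, patients with known disease that is controlled, or treated by a route the form does not list, are recorded as free of it. If some of the 29 centres follow the prose and others the form, the variable also means different things at different centres.

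The second aim of the study is the predictive value of CT-FFR beyond clinical and anatomical factors. Diabetes is an input to both the Framingham and the MESA score, and the Data Analysis section plans multivariable Cox models for MACE. A clinical risk factor recorded with error adjusts less well than it should. What it fails to explain can be credited to CT-FFR if the miscoded patients also differ in CT-FFR and in event risk.

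**Working it through.** The article gives no figure for this point, so there is nothing to reproduce. The check sets the two rules side by side as either/or conditions and finds the patients on whom they differ.

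| Condition | Yes by the Methods if any of | Yes on Table 2 if any of | Methods Yes, form No |
|---|---|---|---|
| Diabetes | history (diagnosed or treated); oral agent; fasting glucose ≥126 mg/dl | oral agent; fasting glucose ≥126 mg/dl | history, no oral agent, glucose <126 mg/dl |
| Hypertension | history; drug treatment; raised pressure (140/90 mmHg) | drug treatment; systolic ≥140; diastolic ≥90 | history, no drug, systolic <140 and diastolic <90 |
| Dyslipidaemia | history; drug treatment; total cholesterol ≥200 mg/dl | drug treatment; total cholesterol ≥200 mg/dl | history, no drug, total cholesterol <200 mg/dl |

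1. **Direction.** For each condition the form's list is the Methods list without the history route. Dropping that route can only turn a Yes into a No, so the form can under-count and cannot over-count.

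2. **Who is affected.** For diabetes, the discordant group is patients on insulin alone or on diet whose glucose is below the threshold. For the other two, it is diagnosed patients without drugs whose measurement is below the threshold, for example a dyslipidaemia shown in LDL-C or triglycerides but not in total cholesterol.

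3. **Who can be recovered.** Insulin-only patients can be identified from Table 3. Diet-controlled diabetics and diagnosed, untreated patients cannot be identified from Tables 1–5.

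4. **Where the error goes.** The listed Framingham inputs are age, sex, total cholesterol, HDL-C, systolic pressure, diabetes, antihypertensive medication and smoking. The MESA inputs include diabetes and lipid-lowering drugs. So only the diabetes item enters the scores. The hypertension and dyslipidaemia items can matter only as covariates in the Cox model.

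5. **Size.** The count would be cohort size × prevalence of diabetes × share on insulin alone or diet × share of those with glucose below 126 mg/dl. Only the cohort size (10,000) is in the article. As illustration only, assume prevalence 20–30%, share on insulin alone or diet 10–20%, and half below the threshold:
   - low: 0.20 × 0.10 × 0.5 = 0.010, or 100 patients
   - high: 0.30 × 0.20 × 0.5 = 0.030, or 300 patients

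   All three inputs are assumptions, and part of this group is recoverable from Table 3. No comparable figure is offered for hypertension or dyslipidaemia.

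**The case against.** The best defence is that the prose is the definition and the form only a collection tool. Insulin is already recorded in Table 3, so an analyst working from the Methods could rebuild most of the diabetes variable. This stands for insulin users. It does not help diet-controlled diabetics or diagnosed, untreated patients, for whom the printed form holds no information. Nor is the mismatch a result of condensing the protocol: the article prints both rules, and they disagree.

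Several stronger readings are tempting, and the article does not support them:

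- *All insulin-treated or diet-controlled diabetics are coded No.* A No also requires glucose below the threshold and no oral agent. The other two conditions likewise need a below-threshold measurement and no drug.
- *All three items distort the risk scores.* Only diabetes is a score input.
- *The lipid values needed for the scores are not collected.* Clinical Variables plans to collect total cholesterol and HDL-C where possible, and computes the Framingham score only for patients with complete information.
- *Prior atrial fibrillation, MI and stroke go unrecorded, so prevalent atrial fibrillation will count as an event.* Eligibility does cover "patients referred for CCTA examination by physicians for the evaluation of suspected or known CAD", and the outcome list reads "Secondary endpoints include cardiovascular death, atrial fibrillation, non-fatal MI, non-fatal stroke". But the Methods list no such history items either, so there is no contradiction. Tables 1–5 are not the whole case report form, since laboratory values are collected that appear in none of them. The article also provides for dating of secondary events and for blinded adjudication that draws on clinical records.

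**Conclusion.** The contradiction is real and holds for all three risk factors. It runs in one direction, towards under-counting, and is confined to patients with a physician history, a below-threshold measurement and no qualifying drug. The size cannot be derived from the article. The 1–3% for diabetes is what the stated assumptions give, not an estimate for this cohort. The effect on the CT-FFR hazard ratio or AUC is likewise unknown. It depends on how many patients are miscoded, how they differ in CT-FFR and event risk, and which covariates enter the model. The point deserves correction because the variables belong to the clinical comparator for the second aim and the remedy is cheap. It does not put the primary endpoint or the study design in doubt.

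**What to change.** - State that the Clinical Variables definitions govern, and add a box for a physician-diagnosed or treated history to the diabetes, hypertension and dyslipidaemia items of Table 2.
- Derive diabetes as Yes if any Table 2 box is ticked, a physician history is present, or Table 3 records insulin or an oral hypoglycaemic agent.
- For patients already enrolled, take the history from medical records and count only diagnoses dated before the baseline CCTA, so that later diagnoses do not leak into a baseline covariate.
- Do not infer hypertension from Table 3 drug classes alone. Beta-blockers, ACE inhibitors, ARBs, calcium channel blockers and diuretics have other indications, and this would add error in the opposite direction.

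The diabetes derivation for insulin users needs only fields already collected. The rest costs three tick boxes and a small amount of record checking. Some histories will not be traceable in the records, and those patients will keep the form's coding.

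### Table 2 records only the site of chest pain, so the angina class counted from the form can be higher, never lower, than the class the text defines (minor)

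*Protocol article*

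**What the plan says.** The Clinical Variables section states that baseline characteristics, clinical symptoms among them, come from an electronic questionnaire and refers to Tables 1–5. It says chest pain is classed by several attributes, including the character of the discomfort as well as its location. It then lists three features:

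- Quality and site together: "a) constricting discomfort in the front of the chest or in the neck, jaw, shoulder, or arm"
- Provocation, with a degree of effort named: "b) induced by excessive physical activity"
- Relief, with a time limit: "c) relieved by rest or nitrates within 5 min"

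All three make typical angina. For the lower classes, "Patients presenting with two of the aforementioned typical angina features are considered to have atypical angina", and "Patients presenting with only one or none of the typical angina characteristics are supposed to have non-anginal chest pain".

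Table 2, item 7, prints three boxes under chest pain:

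- Box 1 gives the site alone: "chest pain: □in the front of the chest or in the neck, jaw, shoulder, or arm"
- Box 2 covers provocation, with no degree of effort named: "precipitated by physical exertion"
- Box 3 covers relief, with the same time limit: "relieved by rest or nitrates within 5 min"

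The third box repeats the text word for word, so the boxes are evidently meant to record features (a), (b) and (c).

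**The concern.** Feature (a) in the text joins two conditions, quality and site. Box 1 keeps the site and drops the quality, and nothing else in Tables 1–5 captures it. A stabbing pain at the front of the chest would fail feature (a) as defined but would satisfy box 1 as printed. The class depends on a simple count with cut-offs at two and three, so one extra tick can change it.

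At stake is whether the published definition describes the data collected. The abstract says clinical characteristics will be analysed for prognostic value, and the second aim is to assess CT-FFR beyond clinical and anatomical factors. If angina class enters such a model, non-anginal pain mixed into the angina classes would tend to dilute their association with MACE. With 29 centers, some staff may also apply the text and others the box, which would add between-center variation to this variable.

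**Working it through.** The plan gives no figure to reproduce, so the check sets the two rules side by side.

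**Step 1. Where the rules can differ.** Take the exertion wording as equivalent in both places, so that only the missing quality matters. The rules then disagree on feature (a) in one situation only: pain at a listed site that is not constricting. The text scores 0 for (a) and the form scores 1.

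**Step 2. Effect on class in that situation.**

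| (b) exertion | (c) relief | Text count and class | Form count and class | Change |
|---|---|---|---|---|
| no | no | 0, non-anginal | 1, non-anginal | none |
| yes | no | 1, non-anginal | 2, atypical | up |
| no | yes | 1, non-anginal | 2, atypical | up |
| yes | yes | 2, atypical | 3, typical | up |

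The form count is never below the text count, so no pattern can move down. On this reading no pattern moves two classes.

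**Step 3. Count over all patterns.** Enumerate site (2 levels) × constricting (2) × exertion (none, ordinary, excessive: 3) × relief (2) = 24 patterns. With any exertion counted as feature (b) under both rules, 5 of 24 move up (3 non-anginal to atypical, 2 atypical to typical), 19 are unchanged and none moves down. These are logical patterns, not patients.

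**Step 4. Can a patient share be given?** The fall in the non-anginal share equals the proportion of chest pains that are at a listed site and non-constricting, multiplied by the proportion of those with exactly one of (b) and (c). If (b) and (c) are independent and each has frequency p among those pains, this is s × (1 − q) × 2p(1 − p), where s is the share at a listed site and q is the constricting share among them. The documents give none of these inputs. Under assumed values:

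- s = 0.95, q = 0.7, p = 0.3: 0.95 × 0.3 × 0.42 = 0.12, or 12 percentage points.
- s = 0.95, q = 0.3, p = 0.4: 0.95 × 0.7 × 0.48 = 0.32, or 32 points.
- s = 0.95, q = 0.5, p = 0.05 to 0.10: 0.475 × 0.095 = 0.045 to 0.475 × 0.18 = 0.086, or 4.5 to 8.6 points.

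All of these also assume that every completer ignores quality. The spread from under 5 to over 30 points is set by the assumptions, so none of these values is an estimate for this study.

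**The case against.** The best defence is that Table 2 is a form printed in a journal article, while the text supplies the definitions by which pain is to be recorded and classed. An investigator who ticks box 1 only for constricting discomfort produces no error, and completion instructions may exist in a fuller document that is not shown. This stands as far as it goes: upward misclassification is possible but not demonstrated. It does not remove the inconsistency, because the article prints both the definition and the form and they disagree. From the completed form alone, no one could tell which rule was applied.

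Four stronger readings are tempting, and the documents do not support them.

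- A reader might infer that the three classes cannot be derived. They can: the boxes map one to one onto the features and the ticks can be counted. What cannot be verified is that the result is the class the text defines.
- A reader might treat the exertion wording as a second loosening. Read literally, with excessive activity as a stricter threshold, 9 of the 24 patterns would move up. But the text never defines excessive, and its preceding sentence speaks only of a relationship with exercise. The difference reads as paraphrase and should not be added to the effect.
- A reader might take one of the assumed percentages above as the size of the problem. The documents contain nothing to anchor it.
- A reader might conclude that the clinical comparator for CT-FFR is weakened. The Data Analysis section names no covariates. Angina class is not an eligibility criterion, not part of MACE, and not among the listed inputs to the Framingham or MESA scores.

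**Conclusion.** The inconsistency is real and minor. Feature (a) requires constricting quality in the text and only site on the form, and pain quality is recorded nowhere in Tables 1–5. Where the form is followed as printed, the class can be one step higher than the definition gives and never lower. This direction follows from the counting rule and needs no assumption about symptom frequencies; it rests on reading the two exertion phrases as equivalent. Whether any patient is misclassified depends on how centers complete box 1, and the number cannot be computed from the documents. The reach is the baseline description and any clinical model that uses angina class.

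**What to change.** Reconcile Table 2, item 7, with the Clinical Variables section: make box 1 record the constricting quality as well as the site, and use one wording for exertion in both places.

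For patients already entered (the study began in November 2019), either report the class as form-derived with a site-based feature (a), or complete pain quality from source records where these are readily available. Full source verification across 29 centers would be out of proportion to the point. A re-analysis on exertion and relief alone is not a substitute, because two features cannot reproduce a rule that counts three.

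The cost is a one-line form change and a sentence in the limitations.
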